There are 2 prior studies which can be used to estimate sample size for the proposed trial. The first was published by Wadhwa et al. in 2001 [26] and the second by Entezary et al. in 2013 [27]. Entezary et al. provides data that is consistent with a more conservative approach, as they used a much lower dose and investigated dextromethorphan for postoperative pain following arthroscopy–an intervention that results in relatively less pain than TKA. Using the smaller effect size from Entezary et al. (*μ* =  − 2.4, *σ* = 5.4) and standard methodology to compare the means using the T statistic with a non-centrality parameter [28, 29], a sample size of 160 patients (80 patients per group) would give 80% power to detect a difference in postoperative opioid consumption with a two-sided Type I error rate of 0.05. In contrast, using the same methodology for the study published by Wadhwa et al. yields a standardized effect size of 0.53, which corresponds to a sample size of 112 patients (56 patients per group). Given these estimates, we plan to recruit a total of 160 patients, which can accommodate 5–10% dropout. However, it should be noted that even if 5–10% of patients are lost to follow-up, the planned recruitment remains conservative. This is because the high doses used by Wadhwa et al. may not have necessarily increased the effect size in their study. In fact, it is possible that the larger dose used by Wadhwa et al. actually negatively impacted their effect size (by increasing adverse events), but these negative effects may have been offset by the fact that TKA is markedly more painful than knee arthroscopy.

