### Assignment of interventions

Randomization will be conducted according to a central computerized randomization schedule (randomizer.at, from Medical University Graz, Austria; Url: http://www.randomizer.at/) with a 1:1 treatment allocation ratio and no stratification factors. The randomization method will be permuted blocks. Blocks of four were used to ensure equal numbers of subjects in each group. A separate investigator that is not involved in the recruitment, treatment, or assessment of participants will generate the allocation sequence and assign participants to the treatment or control group accordingly. Participants and investigators responsible for recruitment and treatment will be blinded. Treatment will be immediately and permanently discontinued and clinical staff will be unblinded if participants experience one or more of the following adverse events thought to be at least possibly related to study treatment: visual hallucinations, delusions, agitation, stupor, coma, respiratory depression, seizures, or any sign of serotonin syndrome.

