This study has several strengths, including adequate power, a randomized, controlled design, and an evidence-based dosing schedule. It will provide the most robust evidence to date on dextromethorphan for postoperative pain control following TKA. However, it is not without limitations. One major limitation is the lack of pharmacokinetic data. Given that there are inter-patient metabolic differences, there will be unaccounted for differences in how much drug each patient is exposed to over time. However, demonstrating clinical improvement despite this limitation has clinical utility, as widespread implementation of dextromethorphan is unlikely to be accompanied by patient-specific dose adjustments. More importantly, for the reasons discussed previously, dextromethorphan remains safe at the chosen dose level. This study effectively excludes the most profoundly sensitized chronic pain patients, as those with a history of opioid abuse and who are unwilling refrain from taking level ≥ 2 analgesics for ≥ 2 weeks prior to surgery are not allowed to participate. While this minimizes heterogeneity, it is not without drawbacks. Given the similarities between the pharmacological properties of ketamine and dextromethorphan, it is possible that chronic or sensitized pain patients are the most likely to show treatment effects. This was demonstrated by Loftus et al. [52] who found that intraoperative ketamine significantly reduced 48-h morphine consumption in patients taking high-dose preoperative opioids but had no effect on 48-h morphine consumption in patients consuming lower doses. At present, the aim of this study is to determine if the standard patient undergoing TKA stands to benefit from dextromethorphan. However, pending results of interim analysis, we recognize that it may be necessary to modify inclusion to allow for (or specifically target) patients with significant pain sensitization. Furthermore, the single-center design will limit the external validity of our findings.

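### The 160 patients needed for 80% power are also the 160 recruited, so 5–10% dropout is not accommodated: power falls to about 75–78%

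*Protocol article*

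**What the plan says.** The sample-size paragraph of the protocol article (Methods, under Participants, interventions, and outcomes) considers two prior studies. It chooses the smaller effect, from an arthroscopy trial, as the more conservative basis: a difference of −2.4 with SD 5.4. On that basis it states that "a sample size of 160 patients (80 patients per group) would give 80% power to detect a difference in postoperative opioid consumption", at a two-sided error rate of 0.05. The second prior study, with a standardized effect of 0.53, is said to need 112 patients (56 per group).

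The paragraph then draws its conclusion: "Given these estimates, we plan to recruit a total of 160 patients, which can accommodate 5–10% dropout". It adds that recruitment stays conservative even with that loss, because the true effect may be larger than the one used. The opening of the same Methods section gives 80 patients randomized to each group, so 160 is the number randomized. The Discussion says: "This study has several strengths, including adequate power"; the abstract makes the same claim.

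**The concern.** A dropout allowance is the gap between the number recruited and the number that must be analysed. Here both are 160. If 160 analysed patients are what 80% power requires, any loss of primary-outcome data takes power below 80% at the chosen effect. The article asserts both properties and the design can have only one of them.

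The stated power is what a reader will use to interpret a null result. If 5–10% of patients provide no primary outcome, the chance of missing the design effect is 22–25%, not the 20% implied. The article also presents adequate power as a strength of the trial.

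**Working it through.** **Inputs, all from the protocol article**

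- Difference 2.4, SD 5.4, so d = 2.4/5.4 = 0.4444 (sample-size paragraph)
- Two-sided α = 0.05, target power 80% (same paragraph)
- Method: "standard methodology to compare the means using the T statistic with a non-centrality parameter" (same paragraph)
- Allocation 1:1 (Assignment of interventions)
- 160 recruited, loss of 5–10% (sample-size paragraph)

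**Step 1. Reproduce the stated figure.**

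Normal approximation: n per group = 2(1.960 + 0.842)²/d² = 2 × 7.849/0.1975 = 79.5, rounded up to 80, or 160 in total. This matches the article.

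Noncentral t: the noncentrality is d√(n/2) on 2n − 2 degrees of freedom. Solving for 80% power gives n = 80.44, so 81 per group. At n = 80 the noncentrality is 0.4444 × √40 = 2.811, the critical value is 1.975, and power is 79.8%.

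The difference between 80 and 81 is immaterial in itself. It shows only that 160 contains no hidden slack and is the number of patients with outcome data that the calculation needs.

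**Step 2. Apply the article's own loss.**

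5% loss leaves 160 × 0.95 = 152 (76 per group). 10% loss leaves 160 × 0.90 = 144 (72 per group).

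| Analysed per group | Power, noncentral t | Power, normal approx. | Difference detectable with 80% power (SD 5.4) |
|---|---|---|---|
| 80 (no loss) | 79.8% | 80.3% | 0.4457 × 5.4 = 2.41 |
| 76 (5% loss) | 77.7% | 78.2% | 0.4574 × 5.4 = 2.47 |
| 72 (10% loss) | 75.4% | 76.0% | 0.4701 × 5.4 = 2.54 |

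**Step 3. What an allowance would have required.**

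- From 81 per group: 81/0.95 = 85.3, so 86 per group (172 in total); 81/0.90 = 90 per group (180 in total).
- From the article's 80 per group: 160/0.95 = 168.4, so 170 in equal groups; 160/0.90 = 177.8, so 178.

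**Step 4. The alternative effect.**

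At d = 0.53, power is 91.5%, 90.1% and 88.5% with 80, 76 and 72 per group. The sample does absorb 10% loss at that effect, but not at the effect for which 80% power is stated.

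**The case against.** Four points can be made for the plan.

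*Little loss is likely at 24 h.* The primary outcome is opioid use at 24 h, and study drug is given only in hospital. The article speaks of loss to follow-up, and its visits run to 3–6 months. A patient who disappears after discharge still contributes to the primary intention-to-treat analysis. This stands as a practical point: actual power may stay close to 80%. But the article does not argue this. It attaches the 5–10% to the sample-size calculation for the primary outcome and says that the sample absorbs it.

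*Choosing the larger of two sample sizes is itself a margin.* 160 exceeds the other estimate by 48, and the second study, in knee reconstruction or replacement, is clinically closer. This stands in part: there is an informal reserve if the true effect is near 0.53. But the article takes the smaller effect as its basis and quotes 80% power for it. It cannot size on the conservative effect and then cover dropout with the optimistic one. Its supporting argument, that dose and pain severity may have offset each other, concerns uncertainty about the true effect and adds no patients.

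*The article never says in one sentence that power remains 80% after dropout.* That is literally so, but in a sample-size paragraph accommodating dropout has no other useful meaning.

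*The shortfall is within the rounding of the inputs.* With 2.35–2.45 over 5.35–5.45, power at 80 per group runs from 77.4% to 82.1%, and at 76 per group from 75.2% to 80.1%. This shows that the 5% case is small. It does not create an allowance, since loss lowers power at every value in that range.

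**Conclusion.** The point holds. At the effect and SD on which the article sizes the trial, 160 patients give 80% power only with no loss of primary-outcome data. Under its own 5–10% loss, power is 77.7% to 75.4% by its named method, a shortfall of about 2 to 5 points. The detectable difference rises from 2.41 to 2.47–2.54.

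This assumes that the lost patients have no 24 h outcome, that loss is equal in the two groups, and that 2.4 and 5.4 are taken as given. If loss falls mainly after 24 h, the true shortfall is smaller. The error is modest in size and does not call the design into question, but the stated property is wrong as written.

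**What to change.** Keep 160 and correct the text. Suggested wording: with 160 patients and no missing primary outcome, power is about 80% for a difference of 2.4 (SD 5.4, two-sided 0.05); if 5–10% of patients lack the 24 h outcome, power is 78–75% for that difference, or 80% for a difference of 2.47–2.54.

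Delete the statement that 160 accommodates the dropout and the statement that recruitment remains conservative. Qualify adequate power in the abstract and the Discussion. If the investigators expect almost complete data at 24 h, they should say so and give the expected rate. The 0.53 result can be reported as a separate scenario (88–90% power after 5–10% loss).

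This costs wording only, and the reported power becomes slightly less favourable. The alternative, holding 80% after loss, means recruiting about 172 (5%) or 180 (10%), that is, 12 to 20 more patients.

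An optional route without more patients is adjustment for baseline covariates fixed in advance. The outcome variance they must explain is 1 − (0.4444/0.4574)² = 0.056 at 5% loss and 1 − (0.4444/0.4701)² = 0.106 at 10%, so about 6–11%. The article gives no figure for how much its listed covariates explain, so this is an assumption.

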### Assignment of interventions

Randomization will be conducted according to a central computerized randomization schedule (randomizer.at, from Medical University Graz, Austria; Url: http://www.randomizer.at/) with a 1:1 treatment allocation ratio and no stratification factors. The randomization method will be permuted blocks. Blocks of four were used to ensure equal numbers of subjects in each group. A separate investigator that is not involved in the recruitment, treatment, or assessment of participants will generate the allocation sequence and assign participants to the treatment or control group accordingly. Participants and investigators responsible for recruitment and treatment will be blinded. Treatment will be immediately and permanently discontinued and clinical staff will be unblinded if participants experience one or more of the following adverse events thought to be at least possibly related to study treatment: visual hallucinations, delusions, agitation, stupor, coma, respiratory depression, seizures, or any sign of serotonin syndrome.

## Data collection, management, and analysis

Demographics and survey data will be entered directly into the Patient IQ database (Additional file 1: Appendix A). Patient IQ has many built-in security features, including off-site backups, an audit trail, secure logins, de-identified data exports, and built-in filtering methods to ensure data quality. Survey answers (clinical outcome data) will be directly entered into the database by the participants themselves (via computer or mobile), which will improve data quality by removing the possibility of transfer errors. Documentation not included in the quantitative analysis of clinical outcomes will be recorded using traditional source documents (Additional file 2: Appendix B). These documents will be kept in the participant’s binder and locked in a secure location. Standard protocols to promote participant retention and ensure follow-up will be implemented. These include, but are not limited to, reminder notifications pushed to participants via the Patient IQ platform and direct correspondence from research staff.

Outcome instruments include standardized assessments of subjective pain (as measured using VAS or NRS 0 to 10), the KOOS, JR questionnaire, the PROMIS-29 questionnaire, and clinical anchors. KOOS, JR is a validated, short-form knee arthroplasty outcomes survey that combines pain, symptoms, and functional limitations into a single score representing overall “knee health” [30]. The PROMIS-29 questionnaire is a set of patient-centered measures that integrates functional limitations, pain interference/intensity, ability to fulfill desired social roles, anxiety/depression, sleep disturbance, and fatigue [30, 31]. PROMIS-29 has been shown to correlate with scales measuring similar constructs for patients with osteoarthritis [32] and, similar to KOOS, JR, is responsive in patients undergoing total joint arthroplasty [33]. Lastly, three clinical anchors (i.e., pain, physical function, and overall change) will be collected with patient-reported outcome (PRO) measures to determine the patient’s global impression of change and validate clinical significance when appropriate. The rationale for the collection and drafting of these anchors has been described at length previously [34–36].

### Monitoring

This is a single-site, investigator-initiated clinical trial and, as such, a formal data monitoring committee will not be utilized. However, the principal investigator, a study monitor, and the lead clinical research coordinator will regularly review study data for the occurrence of mild, moderate, and severe toxicity/adverse events. Mild toxicity/AEs include tachycardia and blurred vision. Moderate toxicities/AEs include visual hallucinations, delusions, stupor, and respiratory depression. Severe toxicity/AEs include coma, seizure, or symptoms concerning for serotonin syndrome. The study will be suspended if more than 1 out of the first 10 patients enrolled in the study group experience moderate or worse adverse event(s) thought to be at least possibly attributable to the investigational treatment.

All adverse events will be recorded in study source documents. Spontaneously reported adverse events will also be reported to the university IRB in accordance with federal and institutional regulations. All serious adverse events thought to be at least possibly related to the study treatment will be reviewed by the PI, a safety monitor (board-certified orthopedic surgeon not directly involved in clinical study activities), as well as lead study coordinator. Adverse events will be identified by regularly reviewing study data. Additionally, the Patient IQ database will automatically notify the independent clinical medical monitor and lead study coordinator when moderate or worse AEs reported. Subjects experiencing serious adverse events will be treated according to the standard of care and followed clinically until their health has returned to baseline status or until all parameters have returned to normal.

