**Fig. 1 Fig1:**
[figure not shown]
Study design flowchart. TKA = total knee arthroplasty; AEs = adverse events; VAS = visual analog scale; KOOS JR = Knee injury and Osteoarthritis Outcome Score for Joint Replacement; PROMIS = Patient-Reported Outcomes Measurement Information System

A standardized, multimodal anesthetic protocol will be implemented. Preoperatively, patients will receive up to 400 mg celecoxib and 1000 mg acetaminophen. Intraoperative anesthetics will include spinal-epidural (15 mg bupivacaine) and propofol (75–100 µg/kg/min titrated to sedation). In the inpatient postoperative setting, oral oxycodone will be available as needed. All pain medications may be adjusted as indicated. All such adjustments will be logged and reported with the final published results.

Participants have the right to withdraw at any point during the course of the study without prejudice. Additionally, the investigator can discontinue participants at any time if medically necessary. Participants may also be withdrawn from the study for the following reasons: (1) concerns for patient safety, (2) noncompliance with study procedures or obligations, or (3) patient withdrawal of consent. In the event that a patient withdraws due to an adverse event thought to be at least possibly related to study treatment, they will be followed until the adverse event resolves or the patient is deemed medically stable by the Principal Investigator. All findings will be documented.

To ensure adherence to intervention protocols, the study drug or placebo will only be administered while the patient is hospitalized for their standard of care treatment. During this time, patients will receive extensive monitoring that is comparable to (or better than) what the standard patient receives when hospitalized for acute medical illness, including a nursing ratio that is equal to or better than 4:1. In addition, dedicated research staff and investigators will be available to ensure all interventions are administered appropriately.

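### The only case review described for a clinician outside the trial's clinical work covers only serious adverse events already judged possibly related to study treatment

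*Protocol article*

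**What the plan says.** All of the following is in the Monitoring section of the protocol article unless another place is named.

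- **No committee:** "a formal data monitoring committee will not be utilized".
- **Case review of serious events:** "All serious adverse events thought to be at least possibly related to the study treatment will be reviewed by the PI". The other two reviewers are the lead study coordinator and "a safety monitor (board-certified orthopedic surgeon not directly involved in clinical study activities").
- **Regular data review:** the principal investigator, a study monitor and the lead coordinator "will regularly review study data for the occurrence of mild, moderate, and severe toxicity/adverse events".
- **Automatic alert:** "the Patient IQ database will automatically notify the independent clinical medical monitor and lead study coordinator when moderate or worse AEs reported".
- **Recording and IRB:** every adverse event goes into the source documents, and spontaneously reported events go to the IRB.
- **Suspension rule:** it counts moderate or worse events among the first 10 patients in the study group, if thought possibly attributable to the investigational treatment.
- **Discontinuation and unblinding** (Assignment of interventions): triggered by a list of events, again only if thought at least possibly related.
- **Concurrent treatment** (Participants, interventions, and outcomes): spinal-epidural bupivacaine and propofol during surgery; afterwards "oral oxycodone will be available as needed".

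**The concern.** An independent reviewer of serious events is useful mainly as a check on the investigator's attribution. Here the attribution comes first and decides whether the reviewer sees the case. An event wrongly judged unrelated is the one that most needs a second opinion, and it is the one this rule leaves out.

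The setting makes such a judgement difficult. The Introduction itself names ventilatory depression and sedation among the side effects of opioids, and the trial watches for respiratory depression and stupor as possible effects of the study drug. Within hours of anesthesia and oxycodone, either event has another plausible cause.

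At stake is case-level safety assessment in a trial that has no data monitoring committee and that the Ethics section classes as greater than minimal risk. The primary efficacy analysis is not affected.

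**Working it through.** The article states no figure on this point, so the check sets the oversight routes side by side and follows one event through them. The event is a serious one that is first judged unrelated to study treatment.

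**Step 1. Which routes depend on relatedness?**

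| Route | Relatedness condition? | Uninvolved clinician stated? | Causality assessment stated? |
|---|---|---|---|
| Case review of serious events | Yes | Yes (safety monitor) | A review is stated |
| Regular review of study data | No | Not stated for the study monitor | No |
| Automatic database alert | No | Yes (independent clinical medical monitor) | No, a notification only |
| IRB reporting | None stated | IRB | No |
| Recording in source documents | No | Not applicable | No |
| Discontinuation and unblinding | Yes | Not stated | Not applicable |
| Suspension rule | Yes | Not stated | Not applicable |

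The event is recorded, is open to the regular data review and may set off the alert. It does not enter the case review, and it does not count under the discontinuation or suspension rules. No row gives it a stated independent causality assessment.

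**Step 2. How far does the alert close the gap?** The article says: "Moderate toxicities/AEs include visual hallucinations, delusions, stupor, and respiratory depression". Respiratory depression, stupor and delusions are therefore graded moderate and should alert the independent monitor whatever their attribution. Three limits remain.

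- No review or judgement is attached to the alert.
- It depends on severity grade, while the case review depends on seriousness. Agitation is on the discontinuation list but not among the graded examples. The wording shows that the grading lists are examples, so this is ambiguity and not exclusion.
- It is generated by Patient IQ. Adverse events are recorded in source documents, and the data collection section describes Patient IQ as holding demographics and survey data.

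**Step 3. Is the relatedness judgement difficult here?** Besides the competing causes, the Discussion gives median half-lives of 2.4 h in extensive and 19.1 h in poor metabolizers, and says that no pharmacokinetic data will be collected. Assuming first-order elimination, the fraction of a dose left after t hours is 0.5^(t / half-life).

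- At 8 h: 0.5^(8/2.4) = about 10%, against 0.5^(8/19.1) = about 75%.
- At 32 h, the interval from the nominal 16 h dose to the 48 h assessment (48 − 16 = 32): 0.5^(32/2.4) = about 0.01%, against 0.5^(32/19.1) = about 31%.

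Timing alone is therefore a poor ground for ruling the drug out when metabolizer status is unknown.

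**Step 4. What would full review cost?** The article gives no serious-event rate. As an assumption only:

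- 160 × 2% = 3.2
- 160 × 4% = 6.4
- 160 × 6% = 9.6

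That is roughly 3–10 serious events in total. The additional reviews would be those among them judged unrelated.

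**The case against.** The strongest reply is that the trial has several safeguards without a relatedness filter. An independent medical monitor is alerted to moderate or worse events, data of all severities are reviewed regularly, spontaneously reported events go to the IRB, and all adverse events are recorded. Also, at least possibly related is a low threshold: a competing cause such as oxycodone does not by itself make the drug impossible as a cause. The study drug is an over-the-counter compound, given three times in hospital under close observation. A condensed article may also leave the causality assessor and the monitors' duties to the full protocol.

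Much of this stands, and it rules out three stronger readings that a reader might infer.

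- **That this is the trial's only outside safety oversight.** It is not, because the alert and IRB reporting also reach people outside the clinical team.
- **That one misattribution removes an event from every safeguard.** It removes the event from the case review and the two rules, but not from recording, regular review or the alert.
- **That an excess of serious events on active drug would go undetected.** Nothing supports this. Adverse events are collected at every post-dose assessment in Table 1 and recorded without a filter, so the arms can be compared.

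That the article does not name the assessor is also not held against it. What survives is a rule that the article states outright: the case review is conditional on attribution. The low threshold reduces the risk of a wrong exclusion but does not remove it, and no other route is stated to supply the missing assessment.

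**Conclusion.** The point holds in a limited form. The only stated case review by an uninvolved clinician is confined to serious events already thought possibly related. The unfiltered routes reduce the gap without being stated to close it. A serious event first put down to opioids, anesthesia or surgery can miss independent case review, and an attribution judgement of the same kind also governs discontinuation and suspension.

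The number of events that would be missed cannot be derived from the article, which gives neither a serious-event rate nor a misattribution rate. The 3–10 events rest on an assumed 2–6% rate and show only that the added work is small. This is an inexpensive safety improvement worth making; it is not a defect that threatens the trial's conclusions.

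**What to change.** In the Monitoring section, replace the sentence on review of serious events with:

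> All serious adverse events, whatever the investigator's attribution, will be reviewed by the PI, the safety monitor and the lead study coordinator; the safety monitor records an independent blinded causality judgement.

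The investigator's attribution stays as a recorded field but no longer decides which cases are reviewed. In the same section, reconcile the titles *study monitor*, *safety monitor* and *independent clinical medical monitor*: state whether they are one role or several.

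The cost is one changed sentence, a clarification of titles, and a few additional case reviews by a monitor already in place. The change secures independent causality review of individual cases. Because that review is blinded, it cannot show an imbalance between arms; that still needs a comparison of the recorded adverse events by arm.
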